### Recruitment {15}

To achieve adequate patient enrolment and reach the target sample size, all centers are encouraged to participate in the current trial. To ensure enrolment of all eligible patients, the study coordinator(s) are in close contact with the local investigators at the participating centers to obtain weekly updates about patients who underwent macroscopically radical PDAC resection. Eligible patients will be contacted by the study coordinators in consultation with the treating clinicians. If an eligible patient is not yet approached for participation in the PACAP or PACOPS project, informed consent for PACAP or PACOPS, including TwiCs and PROMs, will be discussed by the study coordinator(s).

In 2018, 2348 patients were diagnosed with pancreatic cancer in the Netherlands. About 20% (*n* = 470) of these patients underwent macroscopically radical (R0-R1) resection of the tumor. In the Netherlands, all pancreatic resections are performed in centers affiliated with the DPCG, which will all participate in the current study. Based on the current successful enrolment progress, we anticipate that 75% (*n* = 353) of all patients will be registered yearly in the PACAP cohort and that 80% (*n* = 282) of these patients will provide informed consent for the TwiCs design. About 150 patients each year are expected to be included in other studies with a study-specific follow-up, which is an exclusion criterium for the RADAR-PANC trial. This leaves 282 – 150 = 132 patients eligible for randomization in the current study each year. Fifty percent (*n* = 66) of patients will be randomized to a standardized surveillance strategy. We expect that 80% (*n* = 53) of these patients are willing to participate in the intervention arm of the study, with a participation rate of 100% (*n* = 66) in the control arm as a consequence of the TwiCs design. The expected time needed for inclusion of a total of 306 patients (153 patients in each arm) is therefore 28 months. The final analysis will be performed 30 months after the last patient is enrolled.

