### Provisions for post-trial care {30}

Individual patients will remain enrolled in the RADAR-PANC trial for a maximum of 2 years or until patient withdrawal. Follow-up of patients that have completed the 2-year follow-up will be continued for survival information until death. Patients who are withdrawn from the study will be followed-up by a medical specialist or general practitioner for survival information until death. After the study period has ended for an individual patient, continuation of either recurrence-focused or non-standardized follow-up and diagnostic testing is based on shared decision-making between patients and their treating physicians.

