**Fig. 2 Fig2:**
[figure not shown]
Kaplan–Meier curve comparing overall survival between patients with routine follow-up imaging and symptomatic follow-up in the Netherlands between 2014–2019 (unpublished data)

As we expect 80% of patients to accept the experimental intervention offered in the intervention arm of the study, an estimated refusal rate of 20% needs to be taken into account. This leads to a decrease of the overall survival to 29.4 months (80% × 32.0 months + 20% × 19.0 months) for patients in the intervention arm. Moreover, despite that current non-standardized follow-up in daily clinical practice mainly results in a symptomatic follow-up approach without routine imaging, data from our recurrence database showed that 85/1580 patients (5%) did nonetheless receive routine follow-up imaging based on shared-decision making (the remaining 199/284 patients (70%) who received routine follow-up imaging participated in a clinical study with a study-specific follow-up including routine imaging). This results in a slight increase of the suspected overall survival in the control arm to 19.7 months (95% × 19.0 months + 5% × 32.0 months). The clinically relevant survival difference of 29.4 months vs. 19.7 months for the intervention and control arm, respectively, also approximates the mean survival difference of 9.5 months presented in the meta-analysis from Halle-Smith et al. [33]. These numbers correspond to a relative hazard (RH) of survival of 1.49, which is used to calculate the sample size of the study. Furthermore, as we expect a minimal level of loss to follow-up in this surveillance study, a censoring rate of 1% is expected each month.

To detect a 49% overall survival improvement (RH of survival 1.49) for patients in the intervention group, as compared with the control group, with a statistical power of 80% and a 0.05 two-sided significance level, a sample size of 306 patients is required. This calculation was based on the assumption of an exponential model, a median overall survival of 19.7 months in the control arm, a follow-up duration of 30 months, a drop-out rate of 1% and a baseline event rate of 3.5%. Following this calculation, we plan to include 306 patients in total: 153 patients in the recurrence-focused follow-up group and 153 patients in the non-standardized, symptomatic follow-up group.

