### Statistical methods

#### Statistical methods for primary and secondary outcomes {20a}

The latest version of R Studio will be used for statistical analysis.

Baseline characteristics will be reported using standard descriptive statistics. Success of randomization will be evaluated by eye-balling whether the distribution of baseline characteristics between the intervention and control group is even. Primary analysis will be performed according to the intention-to-treat principle. As such, patients randomized to the intervention arm of the trial who refuse recurrence-focused surveillance following the TwiCs design will be analyzed as part of the intervention group. The main study parameter is overall survival, measured as the time from the date of PDAC resection to the date of death. Patients are censored at the time of last known follow-up visit documented if no event occurred. Overall survival rates will be reported as median with 95% CI and will be calculated by the Kaplan–Meier survival curve method. Log-rank test will be used to compare survival between the intervention and control group. One- and 2-year survival probabilities will be calculated. Univariate Cox-proportional hazard analysis will be used to assess the crude effect of a recurrence-focused surveillance strategy on survival. In addition, adjusted effect estimates will be calculated using a multivariable Cox-proportional hazard model, including potential confounders for symptomatic PDAC recurrence. To address potential confounders for which the multivariable analysis needs to be adjusted, a Directed Acyclic Graph was designed on https://www.dagitty.net (Fig. 3). It is hypothesized that a recurrence-focused postoperative surveillance strategy leads to the detection of PDAC recurrence in an asymptomatic stage, which increases the probability to undergo treatment for recurrence, possibly improving survival. The association between postoperative surveillance strategy and overall survival is therefore fully mediated through presence of symptoms at the time of recurrence diagnosis and subsequent administration of recurrence treatment. Given that the median overall survival after resection of PDAC is 21 months and 1- and 2-year survival rates are 75% and < 50%, respectively, we expect that during our follow-up period at least 50% of included patients (*n* = 153) will experience an event. The number of variables included in the multivariable analysis is based on the rule of thumb of ~ 10 events per variable, where a categorical variable counts for the number of categories. Consequently, multivariable analysis is adjusted for 15 baseline covariates that are considered to be the most important, i.e., age (continuous), sex (male/female), and predictors that reflect an (un)favorable tumor biology or treatment course, including performance status (continuous), preoperative CA 19–9 value (continuous), tumor location (head/distal), resection margin status (R0/R1), tumor size (continuous), number of positive lymph nodes (continuous) and tumor differentiation (poor/well-moderate), and administration of adjuvant therapy (yes/no). Given that recurrence treatment is considered a mediator, and not a confounder, no adjustment for recurrence treatment is required. Because administration of neoadjuvant therapy is known to affect preoperative CA 19–9 values, resection margin status, tumor size, and number of positive lymph nodes, neoadjuvant treatment will not be adjusted for. Postoperative complications are deemed to affect the receipt of adjuvant therapy and will thus not be included in multivariable analysis. Results will be presented as hazard ratio’s (HR) with corresponding 95% confidence intervals (CI). A two-tailed *P-*value < 0.05 will be considered statistically significant.

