### Trial status

Protocol version 4.0, October 24, 2023. The first patient was enrolled on March 16, 2021. At the time of submission of this manuscript (January 2, 2024), 219 patients have been enrolled by 7 institutions. Recruitment is anticipated to be completed in April 2024.

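### The final survival analysis is triggered by date alone; with the stated 1% monthly censoring it is expected to have about 77–79% power, and no death count secures the stated 80%

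*Protocol article*

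**What the plan says.** - **Trigger.** Recruitment {15}: "The final analysis will be performed 30 months after the last patient is enrolled". The same section plans 28 months of accrual.
- **Sample size.** Sample size {14} states "with a statistical power of 80% and a 0.05 two-sided significance level, a sample size of 306 patients is required". The model uses exponential survival, a control median of 19.7 months, and "a follow-up duration of 30 months, a drop-out rate of 1% and a baseline event rate of 3.5" per cent. The text before it makes clear that the 1% is per month.
- **Effect.** The same section compares 29.4 with 19.7 months: "These numbers correspond to a relative hazard (RH) of survival of 1.49, which is used to calculate the sample size of the study". The direction is a benefit: "To detect a 49% overall survival improvement (RH of survival 1.49) for patients in the intervention group".
- **Survival tracing.** Provisions for post-trial care {30}: "Follow-up of patients that have completed the 2-year follow-up will be continued for survival information until death".
- **Deaths.** The only event figure is in Statistical methods {20a}: "we expect that during our follow-up period at least 50% of included patients" (n = 153) will have an event. It is used there to decide how many covariates the adjusted model can carry.
- **Interim looks.** Interim analyses {21b} plans none.
- **Actual accrual.** Trial status: the first patient entered on 16 March 2021; by 2 January 2024, "219 patients have been enrolled by 7 institutions"; completion was anticipated in April 2024.

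**The concern.** For a log-rank comparison, the number of deaths determines the power. The number of patients and the calendar matter only through the deaths they produce. The article chooses a calendar rule and names no death count that must be reached, so nothing in it ties the analysis to the stated 80% power.

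Two of its statements also pull the death count in opposite directions. The sample-size model removes 1% of patients per month, while the post-trial section traces survival until death, which suggests lower loss. Which of these proves true decides whether the fixed date falls before or after the point at which 80% power is reached.

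At stake is an analysis held somewhat too early, with an inconclusive result read as no benefit, while further deaths were still being recorded at little extra cost. The article describes the trial as the first randomised one on this question, so a weak null result would carry weight.

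**Working it through.** **Inputs.** From Sample size {14}: two-sided 0.05, 80% power, relative hazard 1.49, control median 19.7 months, 30 months of follow-up, censoring c = 0.01 per month, 153 per arm. From Recruitment {15}: accrual A = 28 months, minimum follow-up F = 30 months. From Trial status: about 37 months of accrual if completed in April 2024; or, extrapolating the average pace, 219/33.6 = 6.52 per month and 306/6.52 ≈ 47 months.

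**Step 1. Deaths needed.** Schoenfeld: 4 × (1.960 + 0.842)² / (ln 1.49)² = 4 × 7.85 / 0.1590 = 197.4, so 198. Freedman's formula gives 203.

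**Step 2. Reproduce 306.** Control hazard λ = ln 2/19.7 = 0.0352 per month, the stated 3.5%. With everyone followed for T = 30 months, the probability of an observed death is P = λ/(λ + c) × [1 − exp(−(λ + c)T)].

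- Intervention hazard *raised*, 0.0352 × 1.49 = 0.0524: P = 0.578 and 0.711, mean 0.644; N = 197.4/0.644 = 306.
- Intervention hazard *lowered*, as stated, 0.0352/1.49 = 0.0236: P = 0.578 and 0.446, mean 0.512; N = 197.4/0.512 = 386 (rounded up).

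So 306 is reproduced only with the effect in the wrong direction. This is the main source of the shortfall below.

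**Step 3. Deaths at the fixed date.** With uniform accrual over A months and minimum follow-up F, and k = λ + c:

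P = (λ/k) × {1 − [exp(−kF) − exp(−k(F + A))]/(kA)}

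For A = 28, F = 30, c = 0.01:

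- Control, k = 0.0452: 0.7787 × [1 − (0.2578 − 0.0727)/1.265] = 0.665; 153 × 0.665 = 101.7 deaths.
- Intervention, k = 0.0336: 0.7025 × [1 − (0.3648 − 0.1423)/0.941] = 0.5365; 153 × 0.5365 = 82.1 deaths.
- Total 183.8.

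**Step 4. Power.** Φ(√d/2 × ln 1.49 − 1.96). For d = 183.8: Φ(6.779 × 0.3988 − 1.96) = Φ(0.743) = 77.1%.

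| Accrual | Loss per month | Deaths at 30 months after last patient | Power |
|---|---|---|---|
| 28 months (planned) | 1% (stated) | 184 | 77% |
| 37 months | 1% | 189 | 78% |
| 47 months | 1% | 194 | 79% |
| 28 months | none | 217 | 84% |

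**Step 5. When 198 deaths are reached, 306 patients.** With 28-month accrual and 1% loss, about 41 months after the last patient, or 11 months past the fixed date. With 37-month accrual and 1% loss, about 37 months. With 28-month accrual and no loss, about 23.5 months.

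**Step 6. The same date with 386 patients.** 193 × (0.665 + 0.5365) ≈ 232 deaths, 86% power (28-month accrual, 1% loss).

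**The case against.** A final analysis at a fixed date with a stated minimum follow-up is an accepted design and not an error in itself. The 30 months in the sample-size model agrees with the 30-month minimum in Recruitment {15}, and staggered entry only adds deaths: 157 if everyone stopped at 30 months, 184 with 28-month accrual. At the stated loss rate the power is steady at 77–79% across the accrual lengths considered. All of this stands, and it limits the point to a modest shortfall.

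It is also fair to say that the shortfall is not independent of the sample-size error. With 386 patients the same date would give about 232 deaths. A reader might infer that the date would fail whatever the sample size; Step 6 shows otherwise.

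Two stronger readings are tempting and do not hold:

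- **That the plan's own figures leave power anywhere from about 70% to 86%.** The low end (157 deaths) censors everyone at 30 months, which Recruitment {15} makes the minimum. The high end (234 deaths) needs zero loss, against the stated 1% per month, and a 47-month accrual that the article does not state.
- **That the plan settles for 153 deaths, which would give 69% power.** That figure is a floor for the events-per-variable rule, neither a forecast nor a trigger.

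A death target might stand in the full protocol or the SAP. That cannot be checked here, but the article does commit to a date as the rule, and that date can be tested against its own inputs.

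**Conclusion.** The point holds as a modest one. With 306 patients, the stated effect and the stated censoring, the fixed date is expected to fall 4 to 14 deaths short of 198 (194 to 184 deaths), giving 77–79% power instead of 80%. If loss is close to zero, the planned 28-month schedule exceeds the target, with 217 deaths and 84%. The outcome therefore depends mainly on a loss rate the date cannot adjust for. The cause is mainly the size of 306. The trigger matters because Trial status shows 219 of 306 patients already enrolled, which leaves the length of follow-up as a practical way to recover the information.

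Assumptions: exponential survival, proportional hazards, uniform accrual, equal loss in both arms, and follow-up counted from enrolment. The 47-month accrual is an extrapolation from the average pace.

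**What to change.** Amend Recruitment {15} so that the final analysis takes place at the later of (a) 30 months after the last patient is enrolled and (b) 198 deaths in both arms combined, up to a pre-specified latest date. The sponsor should choose that date with Step 5 in view.

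The death count should only add to the date and not replace it. If the analysis could run as soon as 198 deaths had occurred and all survivors had passed month 24, then with no loss and 28-month accrual it would come at about month 24 with some 201 deaths (81% power), against 217 (84%) at month 30.

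The survival tracing in Provisions for post-trial care {30} already supplies the data. Only the pooled count need be monitored, so no comparison between arms is made and no alpha is spent.

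If the sponsor keeps the date alone, Sample size {14} should state the expected power at that date: about 77–79% with 1% monthly censoring.

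Cost: a short amendment, a running death count, and a read-out that may move later, by about 11 months with 28-month accrual and 1% monthly loss, and less if accrual is longer or loss is lower.

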### Assignment of interventions: allocation

#### Sequence generation {16a}

The allocation sequence to randomly assign participants into groups is based on computer-generated random numbers, following 2–4-6 variable block randomization, with stratification for institute. Eligible patients are randomized in chronological order.

### Concealment mechanism {16b}

According to the TwiCs design, only participants randomized to the experimental group will be informed explicitly. Patients randomized for the recurrence-focused follow-up will be notified and asked for additional informed consent. In contrast, patients randomized to the symptomatic surveillance (i.e., current clinical practice) will not be informed about their randomization specifically since they have already provided their consent to be randomized and collect their data in a standardized fashion. Consequently, there is no need to conceal participants’ allocation.

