### Who will take informed consent? {26a}

The inclusion and randomization process of the RADAR-PANC trial is schematically shown in Fig. 1. Potentially eligible subjects are identified by the (local) investigator or an authorized delegate, by checking pathology reports of patients with known or suspected PDAC after intended radical resection. The (local) investigator or an authorized delegate will confirm that a potentially eligible patient is included in the PACAP or PACOPS cohort and signed informed consent for being randomized in future studies according to the TwiCs design and participation in quality of life questionnaires. If not, the patient will continue standard of care and will not be randomized for this trial. If the patient meets all the eligibility criteria for the RADAR-PANC trial, the participant is randomized for postoperative surveillance strategy with a 1:1 allocation ratio. Participants are either randomized for follow-up according to the current, non-standardized practice (control), or recurrence-focused surveillance according to the trial protocol (intervention). If the patient is randomized to the control arm, no additional action is taken: patients will receive current standard of care and are not explicitly informed about being randomized to the control arm of the trial according to the TwiCs design. Patients randomized to the intervention arm of the trial will be approached by a researcher and will be offered the experimental intervention within the first 3 to 4 months post-surgery. These patients are informed that they are free to decide whether they want to accept or deny the intervention. Oral and written information is provided and the treating physician is informed. If the patient chooses to participate, the additional informed consent form is signed prior to the start of the intervention.

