### Implementation {16c}

The allocation sequence is computer-generated. The central research coordinator enrolls eligible patients into the study and assigns participants to interventions. Patients who are randomly allocated to the intervention arm are offered the intervention by the research coordinator and asked to provide additional informed consent for participation in the intervention arm of the trial.

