## Assignment of interventions: blinding

### Who will be blinded {17a}

Blinding is not applicable to this TwiCs study. As part of the TwiCs design, however, patients randomized to the control arm and their treating clinicians will not be further notified.

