### Oversight and monitoring

#### Composition of the coordinating center and trial steering committee {5d}

The composition of the trial steering committee at the coordinating center exists of two PhD students from the coordinating center who are responsible for the day-to-day logistics of the trial, including identification of eligible patients, patient inclusion and randomization, and arranging follow-up appointments for patients randomized for the intervention arm. Additionally, they are supervised by an assistant professor and the principal investigator, with whom they meet on a weekly basis and can be consulted for discussion. The coordinating center is responsible for the correct coordination of the trial and providing oversight over all participating centers. The steering committee is assisted by clinicians from the coordinating center (i.e., the Regional Academic Cancer center Utrecht; RAKU), who are involved in the care of pancreatic cancer patients and are present at multidisciplinary team meetings, including surgeons, medical oncologists, radiation oncologists, radiologists, gastroenterologists, and pathologists, are easily accessible for consultation and support.

At each participating center, the local investigator is responsible for the on-site logistics and will appoint an appropriate trial team, which can in part be delegated to the coordinating center. Members of the DPCG will be updated on the trial progress at least during the four yearly DPCG meetings, but can be contacted for consultation, if needed. Radiologists from the participating expert pancreatic cancer center will revise all follow-up CT scans of patients who underwent surgery in their center, if performed elsewhere. In case recurrence is detected, this will be discussed at a multidisciplinary team meeting, functioning as an expert panel for determining study endpoints. Data managers from the coordinating center are responsible for data management, together with the daily trial coordinators.

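### The concealment item is answered by saying that allocation need not be concealed, while the staff who enrol also assign and know past allocations in small, institute-stratified blocks

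*Protocol article*

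**What the plan says.** All places are in the Protocol article.

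- **Concealment mechanism {16b}** explains that only patients allocated to surveillance are informed, and that controls are not, since they consented to randomisation and data collection beforehand. It then concludes: "Consequently, there is no need to conceal" the allocation of participants.
- **Sequence generation {16a}** describes computer-generated random numbers, "following 2–4-6 variable block randomization, with stratification for institute". It adds that eligible patients are randomised chronologically.
- **Who will take informed consent? {26a}** gives the ratio: "the participant is randomized for postoperative surveillance strategy with a 1:1 allocation ratio". It assigns the check of pathology reports and of cohort consent to the local investigator or a delegate.
- **Implementation {16c}**: "The central research coordinator enrolls eligible patients into the study and assigns participants to interventions". Patients allocated to surveillance "are offered the intervention by the research coordinator and asked to provide additional informed consent".
- **Composition of the coordinating center and trial steering committee {5d}** gives two staff members the daily logistics, "including identification of eligible patients, patient inclusion and randomization, and arranging follow-up appointments for patients randomized for the intervention arm".
- **Recruitment {15}** has the coordinators discuss cohort, TwiCs and questionnaire consent with eligible patients who have not yet been approached. It also provides for weekly updates so that all eligible patients are enrolled.
- **Who will be blinded {17a}**: "Blinding is not applicable to this TwiCs study".

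**The concern.** Concealment and blinding are separate safeguards. Blinding concerns who knows the arm after assignment, and this trial cannot have it. Concealment means that whoever decides on entry cannot know or predict the next arm before the patient is irrevocably registered. It is possible in any randomised trial, including one nested in a cohort. The reason given in {16b} bears only on what patients are told afterwards.

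The other sections give the gap practical weight. The role that enrols also assigns and offers the intervention, so it knows earlier allocations. Entry leaves some discretion:

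- A resected patient not yet in the cohort becomes eligible only if someone seeks consent.
- Incapacity to consent is an exclusion that needs judgement.
- Randomisation may take place up to 3 to 4 months after surgery.

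If entry decisions were influenced by the expected arm, the arms could differ in prognosis from the start. Intention-to-treat analysis keeps patients in their randomised arm and cannot undo this. The planned Cox adjustment covers only measured factors, and the plan checks baseline balance by eye.

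**Working it through.** The plan states no figure for predictability, so there is none to reproduce. The question is how well someone who knows all earlier allocations in an institute can predict the next one.

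**Inputs.** Ratio 1:1 ({26a}). Blocks of 2, 4 and 6, stratified by institute ({16a}). Enrolled so far: 219 patients at 7 institutions (Trial status), so 219 / 7 ≈ 31 per institute. *Assumption:* the three block sizes are equally likely, since the article gives no probabilities.

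**Step 1: correct guesses.** The strategy is to guess the arm that is behind and to toss a coin when the arms are level. Completed blocks are balanced, so the running imbalance in an institute equals that in the current block. The guesser therefore does not need the block size. For a block of 2b the expected number of correct guesses is b + 2^(2b−1)/C(2b,b) − 1/2.

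| Block | Expected correct | Share |
|---|---|---|
| 2 | 1 + 2/2 − 0.5 = 1.50 | 75.0% |
| 4 | 2 + 8/6 − 0.5 = 2.83 | 70.8% |
| 6 | 3 + 32/20 − 0.5 = 4.10 | 68.3% |

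Weighted by patients: (1.50 + 2.83 + 4.10) / (2 + 4 + 6) = 8.43 / 12 = 70%. A simulation with 4,000 replicates and 10 to 44 patients per institute gives 69% to 70%. A recruiter who cannot see past allocations or the sequence is right 50% of the time.

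**Step 2: allocations known for certain, current block size unknown.** The guesser knows that blocks are of 2, 4 or 6, but not which is running. Certainty arises only when the observed pattern can come from nothing but a block of 6 with one arm used up. Of the 20 arrangements of such a block, AAABBB and its mirror give 3 certain allocations each, and AABABB and its mirror give 2 each. That is (2×3 + 2×2) / 20 = 0.5 per block of 6, or 0.5 / 12 ≈ 4% of patients. The simulation gives 3% to 4%.

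**Step 3: allocations known for certain, current block size known.** The expected number of forced allocations at the end of a block of 2b is 2b/(b+1), that is 1, 1.33 and 1.5. The share is (1 + 1.33 + 1.5) / 12 ≈ 32% over many blocks. The simulation gives 29% to 31% for 10 to 44 patients and about 30% at 31.

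**Step 4: would larger blocks help?** A block of 8 gives 4 + 128/70 − 0.5 = 5.33 correct, or 67%. A 4-6-8 scheme gives (2.83 + 4.10 + 5.33) / 18 = 68%, about 2 points below the present 70%. At the manuscript's submission it could apply to at most 306 − 219 = 87 patients.

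**The case against.** **The sentence is about notification.** It can be read as saying only that nobody needs to keep a patient's assigned arm secret, and the article is a condensed document. Who holds the list may be set out in the full protocol. This stands to the extent that a missing description of the list holder is not a finding in itself. It does not rescue the sentence, which is offered as the answer to the concealment item and gives a reason that does not bear on it.

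**Stronger readings.** A reader might infer any of the following. The documents support none of them.

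- *That the list is open and every allocation is known in advance.* No section says that anyone who enrols can see it.
- *That the second patient in each block of 2 is certain.* Block sizes vary, so after one allocation the block may be of 2, 4 or 6.
- *That one coordinator screens and judges all exclusions.* The role is held by two supervised people, {26a} gives pathology screening to local investigators or delegates, and CT contraindication follows each hospital's radiology protocol.
- *That selection has taken place.* Nothing in the article shows it.

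**Safeguards exist.** Chronological randomisation bears directly on delaying a patient, and weekly updates on passing one over. Cohort consent is normally sought at diagnosis and is scheduled preoperatively in the participant timeline. Most eligibility criteria are objective. A frail patient allocated to surveillance can also decline and stays in that arm for analysis, which weakens any motive to steer. These points stand as limits. None of them hides the next assignment, and consent from late-approached patients and the judgement of capacity remain open routes.

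**Conclusion.** The point holds as an error in a stated rule that leaves a moderate, avoidable route to selection bias in the overall survival comparison. For a person who tracks allocations within an institute, the next arm is predictable about 70% of the time instead of 50%. About 4% of allocations are certain if the current block size is unknown and about 30% if it is known. These figures assume equally likely block sizes and full knowledge of past allocations at the institute.

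They measure predictability, not bias. The documents give no basis for estimating how many patients could have been steered, in which direction, or with what effect on the hazard ratio. If the sequence was in fact hidden, the sentence misdescribes the trial and needs correcting. If it was not, the exposure is real.

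**What to change.** 1. Delete the sentence in {16b} that says concealment is unnecessary.
2. State there that the sequence, and the order in which block sizes occur, are hidden from everyone who screens, approaches or enrols patients. The set of sizes is already published, so the size of the current block is what can still be protected.
3. For remaining inclusions, release each allocation only after cohort and TwiCs consent and eligibility have been recorded and locked.
4. For patients already randomised, report who could see the sequence.

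The block sizes need not be changed mid-trial: the gain would be about 2 percentage points for at most 87 patients. The cost is a wording amendment and a small change to the randomisation workflow. If recruitment has closed, items 1, 2 and 4 still apply, with item 2 worded as what was actually done.
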